## Abstract

**Background:**

With the global escalation of type 2 diabetes and evidence consistently showing that its onset can be prevented or delayed by changing lifestyle behaviours, there is an urgent need to translate practical, affordable and acceptable interventions from the research setting into the real world. One such approach to lifestyle interventions might be the introduction of a programme in which the individual is provided with choice and facilitated to ‘self-select’ an exercise programme. Previous research has shown that this is likely to be less resource intensive, an essential requirement for success outside the controlled research environment, while at the same time promoting positive responses relating to adherence, competence and self-efficacy, essential attributes for long-term success. Through a two-group parallel-randomised controlled trial, this study aims to assess the clinical and psychological impact of the DEXLIFE ‘self-selected’ lifestyle modification programme in adults at risk of developing type 2 diabetes.

**Methods/design:**

A total of 360 subjects at risk of developing type 2 diabetes are randomly assigned in a 1:3 ratio to a control (*n* = 90) or intervention arm (*n* = 270). Randomization is stratified by age, sex and body mass index. The control arm receives general information on lifestyle and diabetes risk. The intervention group participate in a 12 week ‘self-selected’ supervised exercise training programme accompanied with dietary advice to improve food choices. Participants are given access to Dublin City University Sport (an on-campus gym) and asked to perform four exercise classes per week. Dublin City University Sport offers over 50 classes per week, many of which are medically supervised. If weight loss is indicated, reduction in total calorie intake by 600 kcal/day is advised. Common to all food plans is <10 % saturated fat intake, as well as a dietary fibre intake of >15 g/1000 kcal.

Insulin sensitivity is the primary outcome measure. Secondary outcome measures include glucose function, fitness, body composition, anthropometrics, heart rate variability, lipid profiles, blood pressure, physical activity levels, dietary intake and quality of life.

**Discussion:**

"Self-selected" lifestyle intervention has not previously been evaluated in type 2 diabetes prevention and if shown to be successful could be implemented in practice immediately.

**Trial registration:**

Current Controlled Trials: ISRCTN66987085.

**Electronic supplementary material:**

The online version of this article (doi:10.1186/s13063-015-1042-1) contains supplementary material, which is available to authorized users.

## Background

Patients, physicians, health care organizations and policy planners are struggling with the worldwide rise in the incidence of type 2 diabetes mellitus. Recent decades have seen its prevalence reach epidemic proportions and it is now recognized as the fastest growing chronic disease globally. In 2012, the International Diabetes Federation estimated that more than 370 million people worldwide had diabetes mellitus and that treating it accounted for at least 11 % of total health care expenditures in adults (US $471 billion) [1]. It is anticipated that, unless this exponential increase is slowed or reversed, 592 million people will have diabetes by 2035, with roughly the same number again having prediabetes [1]. Approximately 50 % of these people are undiagnosed and may have diabetes for 5–10 years before clinical identification [1].

It is therefore, not surprising that many of these individuals have diabetes-related complications at the time of diagnosis, with substantially greater risk of mortality and significantly greater treatment costs. Preventing the onset of disease by detecting the risk of progression at an earlier stage and implementing effective prevention programmes is vital in controlling this epidemic. DEXLIFE is an EU FP7 funded project designed to identify biomarkers that better predict the onset of type 2 diabetes in high-risk individuals [2]. A key element to the DEXLIFE project is the implementation of a lifestyle intervention programme that can be used to track changes in biomarkers with risk factors for type 2 diabetes. The design of this intervention had to ensure variation in dietary and physical activity patterns so that identified biomarkers could be applied to everyday life and not just in a controlled research setting.

Large-scale lifestyle modification trials in Europe, the USA and elsewhere have shown that the onset of type 2 diabetes can be prevented or delayed among adults at high risk. The Finnish Diabetes Prevention Study and the US Diabetes Prevention Project revealed a 58 % risk reduction in the progression from impaired glucose tolerance to type 2 diabetes [3–6]. Although great variation in individual responses to dietary modification and exercise training has long been recognized, ‘diet and exercise prescription’ for prevention of diabetes remains largely empirical and much research is required to understand the variation in behavioural and physiological responses to lifestyle modification and to optimally match programmes to individual needs and abilities [7].

Interventions that are delivered through diverse organizations that are embedded in the societal structure and are offered to heterogeneous populations, allowing for individual preferences relating to exercise and diet, are required [8–11]. One such approach to ‘real-world’ lifestyle interventions might involve focusing on the concept of providing choice and facilitating ‘self-selection’ [12, 13]. When self-selection is permitted, the real and perceived rigidity of conventional exercise and dietary guidelines is avoided [14]. It has been shown that by providing choice, an individual’s autonomy is supported and there is an increased perception of control over behaviour [15], resulting in positive adherence, competence and self-efficacy, essential attributes for long-term successful lifestyle change [15, 16].

A systematic review conducted in 2009 [14] examined whether people when ‘left to their own devices’ select exercise intensities that are conducive to cardiorespiratory fitness and health enhancement. A total of 33 studies were included and the overall results showed that self-selected intensity approximated or exceeded the minimum level of the range recommended by the American College of Sports Medicine. Furthermore, from a physiological perspective, self-selected exercise programmes have reported exercise intensities close to the individual’s ventilatory or lactate threshold, resulting in positive physiological improvement [17, 18].

In a similar manner to exercise studies, dietary modification can also improve insulin sensitivity [19, 20] and both are influenced by adherence. Even in individuals who initially achieve a desirable response to dietary restriction, long-term adherence is poor and weight regain can lead to discouragement and, ultimately, discontinuation [21]. Implicit in the concept of adherence is choice and agreed goal setting, treatment planning, and implementation of the regimen. Individuals adhere well when they have been involved in the decision making process, when it makes sense to them and when their preference is taken into account [22]. Highly prescriptive programmes may not be the most successful approach for longer-term health behaviour change; they undermine the individual’s sense of autonomy, generate resistance, do not consider what is important to the individual and do not work in the majority of cases [23]. Facilitating ‘self-selection’ by providing information and guidance may enhance longer-term adherence [22, 23].

To date, there are no large trials investigating the effectiveness of a ‘self-selected’ exercise and dietary lifestyle intervention on individuals at risk of developing type 2 diabetes. The purpose of the DEXLIFE intervention is to determine whether the provision of choice and the facilitation of self-selection is an effective means of reducing modifiable clinical, anthropometric, fitness and psychosocial risk factors associated with the development of type 2 diabetes in high-risk individuals.

## Methods/design

### Study design

The study design is a two-group parallel-randomised controlled trial.

### Setting

The trial is conducted in the Centre for Preventive Medicine, Dublin City University in Dublin, Ireland. The intervention programme is delivered in Dublin City University Sport, an on-campus gym. Dublin City University Sport offers approximately 50 classes per week, varying in intensity and type. This gym is unique in so far as, alongside the usual gym classes such as spinning, aerobics and Pilates (30 classes), it provides a chronic illness rehabilitation programme (MedEx Wellness Programme) that caters for individuals with established cardiovascular disease, diabetes, cancer, heart failure, peripheral vascular disease and pulmonary disorders (20 classes). These programmes are medically supervised and carefully monitored in a casual and friendly atmosphere. Participants in this study could chose to participate in any of the 50 classes on offer [24].

### Hypothesis

The hypothesis tested in this study is that there will be a greater increase in mean change in insulin sensitivity among those participating in the DEXLIFE ‘self-selected’ lifestyle intervention than in those in the control group, who will receive general information on lifestyle and diabetes risk.

### Sample size and power calculation

A 3:1 ratio will be used to randomize a total of 360 participants; 270 to the intervention group and 90 to the control group. We expect a 10 % attrition rate, which will leave 243 and 81 participants in the intervention and control groups, respectively. Based on the effect of lifestyle intervention on insulin sensitivity reported in a previous study [25], we have calculated that, with this sample size and with a power of 0.8, it will be possible to detect a 17 % (equivalent to 0.36 standard deviation) difference in insulin sensitivity between the intervention group and the control group in this study.

### Participants: recruitment and eligibility

Potential participants are identified in three ways. Information sessions are held locally; within the university and in local sports clubs. General practitioners and pharmacists within a 10 km radius of Dublin City University have been contacted and provided with trial information and eligibility criteria and consent forms for potential participants. An online screening tool (FINDRISC) is accessible on the DEXLIFE website. If an individual scores >12, an email is automatically generated to the Dublin City University recruitment team and the potential participant is contacted. Finally, Vhi Healthcare, Ireland’s largest health insurance company, and one of the partners in DEXLIFE, will identify suitable clients from their database of policy holders. Letters will be sent out providing information about the study, together with an invitation to an information session in Dublin City University, where the study is explained in detail by the research team. All potential participants are provided with research study information sheets and consent forms. Once signed consent forms are returned, the Dublin City University research team responds with a phone call, answering any questions relating to the study and scheduling appointments for baseline assessments over the following month.

On the baseline assessments days, the researchers administer a series of clinical, anthropometric, behavioural and psychological tests, measures and surveys, as described in Additional file 1. In addition, sociodemographic data on age, sex, self-reported ethnicity, occupational status, educational attainment and marital status, family history of diabetes or cardiovascular disease and lifestyle (smoking, alcohol consumption, physical activity levels and dietary intake) are collected. Additional file 2 outlines the movement of the participants through the stages of recruitment to the study. Following the baseline health assessments, eligibility for the study is determined on the following criteria.

#### Inclusion criteria

Adults, aged between 18–75 years, who report a sedentary lifestyle (<150 minutes physical activity per week) and show at least one of the following diabetes risk factors are eligible to participate:Impaired fasting glucose (fasting plasma glucose levels >5.6 to <7 mmol)Impaired glucose tolerance (two-hour plasma glucose levels of >7.8 to <11.1 mmol)FINDRISC questionnaire score >12 (1 in 6 chance of developing type 2 diabetes in the next 10 years)

#### Exclusion criteria

At the time of recruitment, individuals who have any of the following are not eligible to participate in the study: (i) type 2 diabetes mellitus; (ii) severe cardiovascular, respiratory or renal disease; (iii) active cancer; (iv) neuromuscular, musculoskeletal or rheumatoid disorders exacerbated by exercise; (v) peak aerobic capacity >50 ml/kg·min; (vi) >5 % decrease in body weight in the previous 3 months or (vii) significant cognitive or mental illness.

### Randomization process

An allocation sequence is obtained using the RALLOC command implemented in the statistical software package STATA/IC 12.1 (StataCorp LP, USA) and used to randomize eligible participants in a 3:1 ratio to intervention (DEXLIFE ‘self-selected’ lifestyle programme) or control. Randomization is stratified by age, sex and body mass index using random blocks of four, to ensure a balance of participant characteristics in each group. Participants will be randomly allocated to either intervention or control by the project manager according to the allocation sequence. Because of the nature of the intervention, neither the participants nor the research team are blinded to allocation.

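### A single stated block size of four at 3:1, in an open single-centre trial, lets anyone tallying past allocations know up to 43.75% of assignments in advance

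*Protocol article*

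**What the plan says.** Under Randomization process, the protocol article says that a computer-generated sequence is "used to randomize eligible participants in a 3:1 ratio to intervention" or control. It continues that allocation is stratified by age, sex and body mass index, "using random blocks of four, to ensure a balance of participant characteristics in each group". No other block size is mentioned.

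The same section says how allocation is carried out: "Participants will be randomly allocated to either intervention or control by the project manager according to the allocation sequence". It adds that "neither the participants nor the research team are blinded to allocation".

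The Setting section makes this a single-centre trial: "The trial is conducted in the Centre for Preventive Medicine, Dublin City University in Dublin, Ireland". Under Participants: recruitment and eligibility, the university research team telephones people who have returned consent forms and books their baseline visits. The section then says: "Following the baseline health assessments, eligibility for the study is determined on the following criteria". Most entry criteria are numeric, but the Exclusion criteria section also lists some that call for judgement, such as disorders made worse by exercise and significant cognitive or mental illness.

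**The concern.** At 3:1, a block of four always contains three intervention places and one control place. Once the control has appeared, every remaining place in that block is intervention; after three interventions, the next place must be control. Nobody needs to see the list to work this out. The block size, the ratio and a record of earlier allocations in the stratum are enough, and in an open single-centre trial one team is in a position to have all three.

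Foreknowledge matters only if someone who has it can affect who enters or when. Here the team contacts candidates and schedules baseline visits, and eligibility is settled after staff have met and measured the candidate. The intervention asks for four exercise sessions a week, so staff may form a view on who would suit it. If more motivated candidates were timed or steered into the exercise arm, the comparison of insulin sensitivity would be tilted, and adjustment for measured baseline variables would not fully remove the effect of motivation or likely adherence.

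**Working it through.** **The plan's own figure.** The article gives no figure for predictability. Its sample size section states: "A 3:1 ratio will be used to randomize a total of 360 participants; 270 to the intervention group and 90 to the control group". That agrees with the ratio (360 × 3/4 = 270; 360 × 1/4 = 90). With 10% attrition, leaving 243 and 81, and a difference of 0.36 SD, and assuming a two-sided alpha of 0.05 (not stated):

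- 0.36 × √(243 × 81 / 324) = 0.36 × √60.75 = 2.806
- 2.806 − 1.960 = 0.846, so power = 0.801

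The stated power of 0.8 reproduces. The block size does not enter it.

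**Inputs for the check.** Ratio 3:1, block size 4 and no blinding of the research team come from Randomization process; the single centre comes from Setting. Blocks are taken to be randomly permuted blocks of size four. The observer is assumed to know the block size and to keep a tally for each stratum.

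**Assignments known for certain.** An assignment is certain when all places left in the block belong to one arm. The control is equally likely to be in each of the four positions:

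| Control in position | Certain assignments | of which control |
|---|---|---|
| 1 | 3 | 0 |
| 2 | 2 | 0 |
| 3 | 1 | 0 |
| 4 | 1 | 1 |
| Mean | 7/4 = 1.75 | 1/4 = 0.25 |

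- All assignments: 1.75/4 = 43.75%
- Intervention: (1.75 − 0.25)/3 = 1.5/3 = 50%
- Control: 0.25/1 = 25%, which is 0.25/4 = 6.25% of all assignments

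If all 360 participants fell in completed blocks there would be 90 blocks, and 90 × 1.75 = 157.5 assignments would be certain on average.

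**Incomplete blocks.** By position in the block, the chance that an assignment is certain is 0, 1/4, 1/2 and 1. A stratum of 10 has two full blocks and two further places: (2 × 1.75 + 0 + 0.25)/10 = 37.5%. Incomplete blocks always lower the share, so 43.75% is the upper figure.

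**Gain over the base rate.** Always guessing intervention is right 75% of the time under any 3:1 scheme. Guessing intervention until the block forces otherwise is right for 3, 3, 3 or 4 of 4 as the control falls in position 1, 2, 3 or 4. The mean is 13/4 = 3.25, and 3.25/4 = 81.25%, a gain of 6.25 percentage points.

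**Alternatives.** The same enumeration gives 28.6% certain for fixed blocks of 8 and 21.25% for fixed blocks of 12. A simulation with sizes 4 and 8 drawn at random, where the observer knows the two possible sizes but not which was drawn, gave about 8% for a stratum of 10 and 10.5% for a stratum of 90.

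**The case against.** Several points on the other side are sound.

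- **Concealment.** A reader might infer that, because the project manager allocates from the sequence, the list is open to those who enrol and all assignments are known to them. The article does not support that. It does not say that the project manager recruits, judges eligibility or sees upcoming assignments, nor that there is no controlled release of the list. A journal article commonly leaves such mechanics to the full protocol. This stands, and nothing here rests on who holds the list.
- **Wording.** The word random could be meant to say that block sizes vary. That is possible, but the sentence names four and nothing else, so permuted blocks of size four is the natural reading.
- **Conditions on 43.75%.** It needs someone who knows the block size and the stratum boundaries and keeps a running tally. Being unblinded makes this feasible but does not show that anyone does it. This stands.
- **Small gain.** Most certain assignments are interventions, which are likely in any case, and the gain in correct guesses is 6.25 points. This stands and limits the weight of the point.
- **Existing protections.** Consent and baseline assessment come before eligibility is decided, eligible participants are then randomized, most criteria are numeric, and ANCOVA is planned. These reduce the scope for steering but do not remove it, because timing and the judgement criteria remain.
- **Timing.** Trial status expects recruitment to finish by September 2015, so few participants may be left to randomize. The article does not say how many.

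One possible reply does not succeed: hiding the list would not by itself cure the problem, because the tally uses past allocations only.

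**Conclusion.** The point holds as a modest, conditional weakness of design. As stated, the scheme uses the smallest possible block at 3:1 in an open trial at one centre. For an observer who knows the block size and tracks each stratum, up to 43.75% of assignments are certain in advance. This rests on reading the sentence as permuted blocks of size four and on blocks being completed; the stratum sizes are not given, so the shortfall from incomplete blocks cannot be fixed exactly.

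Selection bias is therefore possible. The article does not show that it occurred, and no direction or size of bias in insulin sensitivity can be derived from it.

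**What to change.** For participants still to be randomized, generate the remaining stratified list with randomly varying block sizes in multiples of four, for example 4 and 8, and do not disclose the sizes to staff who recruit or judge eligibility. On the figures above, this lowers the share of certain assignments from about 38–44% to about 8–11%.

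The cost is one regenerated list. The downside is slightly looser balance within small strata, which adjustment for age, sex and body mass index in the analysis covers. Participants already randomized are unaffected, so the benefit depends on how many remain.

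If block sizes already vary, no new list is needed; correct the sentence under Randomization process so that it no longer gives four as the only size.

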### Description of intervention and control groups

#### Intervention

The DEXLIFE lifestyle intervention is a 12 week ‘self-selected’ supervised exercise training programme accompanied with dietary advice, with an overall aim of increasing insulin sensitivity. Each participant is given access to Dublin City University Sport (an on-campus gym) and asked to perform four moderately intense exercise sessions (45–60 minutes) per week. Rather than performing individualized programmes, participants are encouraged to join group fitness classes. Dublin City University Sport offers over 50 classes per week, many of which are medically supervised. The majority of classes combine dynamic cardiovascular and resistance exercises. These classes offer a safe environment to all participants, particularly older participants, who may be unfamiliar with a gym environment and nervous about exercising for the first time, and who may require a little more support from both a social and a medical perspective. Participants are free to self-select and attend any of the available classes in Dublin City University Sport that they feel best suit their daily routine, exercise preference and ability. Participants are encouraged to attend the gym for all exercise sessions. When this is not feasible, exercise programmes are performed at home with remote support from the DEXLIFE team in Dublin City University.

A 3 day estimated food diary is used to assess dietary intake. Once completed, the participant meets with a dietician together review the diary, identifying unhealthy food choices and develop a plan to modify these choices. If weight loss is indicated, reduction in total calorie intake by 600 kcal/day is advised. A detailed review of the dietary record is performed with the participant and healthy alternatives or suggestions are provided to replace unhealthy components of the diet. Common to all food plans is <10 % saturated fat intake as well as a dietary fibre intake of >15 g/1000 kcal, irrespective of whether weight loss is a requirement or not.

To optimize adherence, an exercise diary, pedometer and regular follow-up telephone contact are utilized. Individuals are asked to record all exercise sessions in an online diary, providing details of the type, time and intensity of exercise completed. A pedometer is given to all participants, so that they can record daily number of steps and number of steps per specific exercise session if they are completing their exercise sessions at home The exercise diary is closely monitored by the research team and contact is made if the diary is not been completed for more than a couple of days.

